## Abstract

**Background:**

Patients undergoing gynaecological surgery are known to experience anxiety. While the use of music selected by patients based on their personal taste has hardly been evaluated, a recent study suggests that musical preferences significantly alter the anxiolytic and relaxing effects of music. Our study aims to determine whether self-selected music decreases patient anxiety prior to gynaecological surgery, as compared with predetermined music from a software programme such as MUSIC CARE®.

**Methods:**

The study will consist of a clinical trial comparing the effects of self-selected music versus predetermined music on patient anxiety prior to gynaecological surgery. A minimum of 170 patients will be randomised in a 1:1 ratio. Inclusion criteria will be: women aged 18–55 years, awaiting scheduled gynaecological surgery under general/local anaesthesia or under sedation; having created a personal 20-min playlist; and not having received anxiolytic drugs prior to surgery. The primary outcome will be the difference between the preoperative anxiety score taken 15 to 20 min before the music-listening session and the preoperative anxiety score taken shortly after the session, as measured with the STAI for state anxiety.

**Discussion:**

This study should help to identify more effective non-medical treatments for preoperative anxiety, as well as to adapt music therapy to the cultural context of patients.

**Trial registration:**

ClinicalTrials.gov, ID: NCT03226834. Registered on 24 July 2017.

## Background

Anxiety is a physiological and psychological state characterised by somatic, emotional, cognitive, and behavioural components. Surgical procedures and preoperative wait are anxiety-provoking situations [1]*.* It is estimated that the incidence of preoperative anxiety ranges from 60 to 80% [2, 3]. A high level of anxiety can lead to an increase in heart and respiratory rates, blood pressure, cortisol levels, and feelings of fear and uncertainty [4, 5]. It can also hinder the wound healing and immune system response, increasing risks of infection and postoperative complications [1]. Stress and anxiety are especially high among patients who have learned that they must undergo gynaecological surgery, as the latter comes with a high risk of partial or complete removal of one or more organs associated with motherhood or femininity [6].

In preoperative settings, it is common practice to prophylactically administer sedative or anxiolytic drugs in order to reduce patient anxiety. Yet, these treatments often cause side effects like drowsiness and breathing difficulties, and they can interact with anaesthetic agents by prolonging awakening duration and hospital stay [7]. In view of this, non-medical strategies such as music therapy, hypnosis, acupressure, and sophrology are increasingly used to reduce preoperative anxiety. In parallel, research on music therapy has grown exponentially over the last 20 years [1, 8]. Randomised controlled trials (RCTs) have highlighted the anxiolytic effects of music therapy in surgery [9–12], cardiology [13–15], and oncology [16, 17]. Moreover, a 2013 systematic literature review has presented a meta-analysis of 26 trials covering a total of 2051 participants, which suggests that listening to music has beneficial effects on preoperative anxiety compared with routine care alone [1]. In 2018, another systemic review examined the effectiveness of music as an adjunct treatment in anxiety for patients undergoing hip and knee surgery and showed that music improved anxiety in six of the ten studies [18].

Nevertheless, most published RCTs evaluate the effects of music therapy on preoperative anxiety by comparing patients who listen to researcher-selected or predetermined music (from a software programme such as MUSIC CARE®) with patients who listen to no music at all. The effects of self-selected music on patient anxiety have hardly been investigated [19, 20]. One exception is a recent study on the anxiolytic and relaxing effects of music, which has highlighted the importance of preference and familiarity in eliciting the relaxation response [21].

Perceptions of music styles, rhythms, and sounds are known to vary depending on cultural background, ethnicity, and personal experience. However, music therapy in preoperative settings currently relies on software programmes that provide pre-selected, standardised music playlists. This is the case of MUSIC CARE®, the music therapy programme that has been in use in our gynaecology department for the past 10 months. Though the efficacy of MUSIC CARE® has been demonstrated, the playlists it provides (jazz, classical music, world music, etc.) are not totally adapted to the specific cultural contexts of users. For example, in Reunion Island, a French overseas territory with a multiethnic and multicultural population, two popular music styles are *Séga* and *Maloya*. This type of music is not included in MUSIC CARE® software.

Our study seeks to fill this gap by letting patients create their own, culturally adapted, music playlist. Our assumption is that a self-selected playlist composed of patients’ preferred songs will have beneficial effects on preoperative anxiety.

The aim of our study is to determine whether listening to self-selected music decreases patient anxiety as compared with predetermined music from a software programme such as MUSIC CARE®. To do this, we will conduct a parallel, superiority, RCT comparing the effects of self-selected music versus predetermined music on patient anxiety prior to gynaecological surgery.

## Methods: participants, interventions, and outcomes

### Study setting

This study will be a monocentric, parallel, superiority, RCT conducted in the Gynaecological Surgery Department of Reunion Island Hospital. Patients will be randomly allocated to one of two groups: one group will listen to self-selected music and the other to predetermined music.

### Eligibility criteria

#### Inclusion criteria

Inclusion criteria will be as follows: women aged 18 to 55 years; awaiting scheduled gynaecological surgery under general/local anaesthesia or under sedation; not having received anxiolytic drugs prior to surgery; having a good understanding of French; knowing how to read and write; having signed an informed consent form. To be included in the study, patients will need to have created a personal 20-min playlist for the study.

#### Exclusion criteria

Exclusion criteria will be as follows: having severe hearing loss or speech impairment; being deprived of liberty by judicial or administrative decision; being under trusteeship or guardianship; suffering from dementia; having a history of anxiety or depression; suffering from neuromotor disabilities; undergoing emergency or ambulatory surgery.

### Intervention

#### Intervention group

Patients will listen to the music playlist they will have created at home based on their personal taste. The equipment used will vary according to the patient: a smartphone, a touchpad, a computer, or a CD player.

#### Control group

Patients will listen to a predetermined music playlist that they will have chosen among those available on the MUSIC CARE® software. Patients can choose among 25 playlists, including reverie, Cuban night, guitar ballad, film scores, folk guitar, etc.

MUSIC CARE® is a non-drug alternative for the management of anxiety and pain that uses a form of music therapy known as the ‘U sequence’. The latter is based on the hypno-analgesia principle, whereby progressive variations in tempo, rhythm, tune, and harmony bring patients into a state of deep psycho-muscular relaxation before the awakening phase. The objective of MUSIC CARE® is to promote wellbeing and to induce a relaxed state in patients by loosening their muscles and reducing their level of anxiety or pain.

The U sequence is only for the control group and is composed of three phases:Sleep-inducing phase (stimulating rhythms), which corresponds to the patient’s current state of consciousnessRelaxation phase (slow rhythms)Awakening phase (moderate rhythms), which signals the end of the session

#### For each group

An inclusion visit will take place the day before surgery. During this visit, the investigator will provide detailed information on the study and answer the patient’s questions concerning the objectives, constraints, foreseeable risks, and perceived benefits of the study. The investigator will also be responsible for obtaining written informed consent from the patient.

During the inclusion visit, a department nurse or care provider with training in MUSIC CARE® will explain the software to the study participant. Each patient will be asked to choose a predetermined music playlist from those available on the MUSIC CARE® software. The following day (i.e. the day of surgery), participants in the control group will be asked to listen to this music playlist, while those in the intervention group will be asked to listen to the music playlist they will have created at home. There will be only one music-listening session in the hour preceding surgery. The session duration will be 20 min. To ensure that patients do listen to a music playlist, a trained research team member will bring a MUSIC CARE® tablet to each patient, notify her of the group to which she has been allocated, and inform her that she can start listening to the music playlist on the support of her choice. After 20 min, the research team member will return to inform the patient that the session has ended and will recover the equipment. All the interventions for each group are summarised in Figs. 1 and 2. During the music-listening session, patients will be alone in their individual room, seated in an armchair or lying in the supine position. They will not be disturbed by anyone. The music will be played through headphones with disposable foam ear cushions to avoid nosocomial infection, and there will be no limit on volume levels. Patients will be reminded that they can listen only to the MUSIC CARE® playlist or the self-selected playlist (and to nothing else) during the session. The care team will be blinded to patient randomisation.

**Fig. 1 Fig1:**
[figure not shown]
Standard Protocol Items: Recommendations for Interventional Trials (SPIRIT) Figure: schedule of enrolment, intervention, and assessments

**Fig. 2 Fig2:**
[figure not shown]
Diagram to show the timing when each outcome take place

If a patient receives anxiolytic drugs the day before or the day of surgery, she will be withdrawn from the trial. All patients will receive routine care.

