### Sample size

According to a meta-analysis published in 2013, the average preoperative STAI anxiety score reported in the literature is 43 ± 8. However, this score is 38 + 8 in patients who listen to music prior to surgery compared with patients who receive conventional care alone [1]. Our study hypothesis is that there will be a further decrease of 3 points in the intervention group compared with the control group. This difference will be considered clinically relevant. Furthermore, we posit an intra-individual correlation equal to 0.5 between the measure taken before the music-listening session and the measure taken after the session (conservative assumption). Under this hypothesis, the inclusion of 85 patients in each group (170 in total) will highlight a significant difference in anxiety reduction between the control group (6-point decrease) and the intervention group (9-point decrease), with an alpha level of 5% and a statistical power of 80%.

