## Methods: Assignment of interventions

Eligible patients will be randomised on the day of surgery using EnnovClinical®. Randomisation will be balanced in both groups, single-blinded, with a 1:1 allocation ratio, without stratification. The patient will know her allocation to the control group or to the intervention group, but the care-giver team will be unaware of it. The randomisation list will be established by the statistician from the methodological support department before the start of the research. The method used will be a randomised block approach, using the SAS® Proc Plan. We will build blocks of variable size. The investigator will perform the randomisation directly via the electronic case report form (eCRF) using the CS Random module of the Ennov Clinical® eCRF the day of surgery.

Routine care providers and care team members performing outcome assessment visits will be blinded to the patients’ group allocation. Only the research team will be aware of the group to which patients have been allocated. ‘Do Not Disturb’ signs will be placed on patient room doors during the listening session. Patients will be warned not to mention their group allocations to care providers.

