#### Primary outcome assessment

Anxiety scores measured after the music-listening session will be compared between the two groups, using an analysis of covariance model (ANCOVA) adjusted to the group and to the anxiety score measured before the music-listening session. This method is recommended for analyses of RCTs that evaluate a variation between an initial value and a post-intervention value.

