#### Secondary outcomes assessment

Comparisons of VAS values and physiological parameters between the two groups will be performed using the same method as will be used for the primary outcome. Comparisons of immediate post-surgical pain and hospital length of stay between the two groups will be performed using the Student’s *t* test or the Mann-Whitney *U* test, as appropriate.

An intention-to-treat and per-protocol analysis will be conducted. Subgroup analyses considering anxiety, pain, physiological parameters, and length of stay by type of surgery will be performed.

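### The anxiolytic withdrawal rule runs past randomisation and past the post-session STAI; read plainly, it conflicts with the intention-to-treat analysis and can bias the comparison towards no difference

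*Protocol article*

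**What the plan says.** - **Withdrawal rule** (Intervention, For each group, text after Fig. 2): "If a patient receives anxiolytic drugs the day before or the day of surgery, she will be withdrawn from the trial". The text does not say whether data already collected are kept, or at what hour the rule stops applying.
- **Entry criterion** (Inclusion criteria): "not having received anxiolytic drugs prior to surgery". The same section admits patients "awaiting scheduled gynaecological surgery under general/local anaesthesia or under sedation".
- **Randomisation** (Methods: Assignment of interventions): "Eligible patients will be randomised on the day of surgery using EnnovClinical".
- **Session** (For each group): "There will be only one music-listening session in the hour preceding surgery". State anxiety is measured 15 to 20 min before it and shortly after it (Outcomes).
- **Primary analysis** (Primary outcome assessment): the post-session scores are compared "using an analysis of covariance model (ANCOVA) adjusted to the group and to the anxiety score measured before the music-listening session".
- **Analysis sets** (Secondary outcomes assessment): "An intention-to-treat and per-protocol analysis will be conducted".
- **Sample size**: "the inclusion of 85 patients in each group (170 in total) will highlight a significant difference in anxiety reduction". No rate of loss or withdrawal is mentioned. The Abstract calls 170 a minimum.

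**The concern.** An anxiolytic given later on the day of surgery can come after randomisation. A likely reason for giving one is anxiety that the music did not relieve, which is what the primary outcome measures. If such patients leave the trial, those who responded least are removed. Should one kind of music work better, more would be removed from the other arm, even with a care team that does not know the allocation.

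Three things are at stake. The analysis labelled intention-to-treat might not contain all randomised patients. The estimated difference could be pulled towards zero. Pain and length of stay, which are measured after surgery, might never be collected for withdrawn patients, and no later analysis plan can recover them.

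**Working it through.** **1. The timing, set side by side.**

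| Anxiolytic given | Status | Consequence |
|---|---|---|
| Day before, or that morning before randomisation | Ineligible under the entry criterion | No bias in the randomised comparison |
| After randomisation, before the session | Post-randomisation | If the trigger is only the anxiety captured by the pre-session score, that score is the ANCOVA covariate and no bias follows |
| After the post-session STAI | Post-randomisation, primary outcome already recorded | Bias if the recorded data are discarded and the trigger is post-session anxiety |

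The rule as worded covers all three rows.

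**2. Reproducing the 85 per group.** Inputs from Sample size: difference 3, SD 8, correlation 0.5, alpha 5% (taken as two-sided; sidedness is not stated), power 80%.

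- ANCOVA residual SD = 8 × √(1 − 0.5²) = 6.93, so the variance is 48.
- n = 2 × (1.96 + 0.842)² × 48 / 3² = 83.7, hence 84 per group by the normal approximation.
- The noncentral t distribution gives exactly 85, with power 80.1%.

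The stated figure is therefore the ANCOVA requirement with no allowance for loss.

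**3. Power if patients are excluded.** The loss rates are assumptions. Power is by the normal approximation at 85 × (1 − d); the last column is 85 / (1 − d), rounded up.

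| Loss d | Evaluable per group | Power | Per group to keep 85 |
|---|---|---|---|
| 0% | 85 | 80.6% | 85 |
| 2% | 83.3 | 79.8% | 87 |
| 5% | 80.75 | 78.6% | 90 |
| 10% | 76.5 | 76.4% | 95 |
| 15% | 72.25 | 74.0% | 100 |
| 20% | 68 | 71.4% | 107 |

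With whole patients and the noncentral t, the values are slightly lower: 78.2% at 81 per group and 75.6% at 76.

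**4. Bias.** One million patients were simulated: pre-session mean 43, SD 8, correlation 0.5, control post-session mean 37 (the plan's 6-point decrease), true difference -3. Patients were removed by one of three mechanisms and the ANCOVA was refitted. Without removal the estimate is -3.00. The graded mechanism uses a logistic probability with slope 0.15 per STAI point.

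| Removed overall | Highest post-session scores: control / intervention removed, estimate | Graded dependence on post-session score: control / intervention removed, estimate | Highest pre-session scores: estimate |
|---|---|---|---|
| 5% | 6.8% / 3.2%, -2.57 | 6.0% / 4.1%, -2.88 | -3.0 |
| 10% | 13.2% / 6.8%, -2.32 | 11.7% / 8.2%, -2.79 | -3.0 |
| 20% | 25.1% / 14.9%, -1.97 | 22.8% / 17.1%, -2.68 | -3.0 |

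A second run with control post-session mean 38 and fixed cut-offs agrees. Removal at a post-session STAI of 48 or more (10.6% control, 5.3% intervention) gives about -2.4. Removal at 46 or more (15.9% and 8.5%) gives about -2.2.

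**The case against.** The strongest reply is that withdrawal from the trial need not mean deletion from the analysis. The protocol plans both an intention-to-treat and a per-protocol analysis, medicated patients fit naturally in the distinction between the two, and detailed set definitions are commonly left to an analysis plan. Where post-session anxiety triggers the drug, the primary outcome already exists, so bias requires that it be thrown away. Where the trigger is pre-session anxiety, ANCOVA deals with it. A trigger during the session is less plausible, since the patient is alone and undisturbed for 20 min. The care team is to be blinded, patients with a history of anxiety or depression are excluded, and no anxiolytic rate is given. The number 170 is described as a minimum.

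Much of this stands, and it rules out several stronger readings. A reader might infer that an intention-to-treat analysis is impossible; that follows only if withdrawn patients are also dropped from analysis, which the text does not say. A reader might infer that every withdrawal under the rule is a post-randomisation exclusion; those before randomisation are plain ineligibility. A reader might also infer that drugs given for procedural sedation trigger the rule; the text leaves this open.

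What does not fall away is the rule itself. It is stated, not omitted, and its plain sense is that participation ends. Blinding the care team does not prevent selection on visible anxiety: a nurse administers the STAI and reads the VAS before the patient goes to the operating room. Calling 170 a minimum commits the trial to no particular allowance.

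**Conclusion.** The point holds as a conflict between a stated rule and a stated analysis. Followed as written, the rule can remove randomised patients for a reason tied to the primary outcome, including patients whose post-session STAI is already complete.

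Its size is conditional. Removing 5% to 20% of patients according to post-session anxiety would shrink a true difference of -3 to between about -2.9 (graded dependence) and -2.0 (strict threshold). Removal on pre-session score alone would not bias the ANCOVA. These rates and mechanisms are assumptions, so bias is not shown to occur. A reader might fear a falsely positive trial; in every biased scenario the shift is towards zero, so the danger is missing a real benefit. The loss of power from numbers alone is modest: about 78.6% at 5% loss and 76% at 10%, against 80.1% to 80.6% with none, depending on the approximation.

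**What to change.** Reconcile the entry criterion, the withdrawal rule and the sentence on analysis sets:

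1. Treat an anxiolytic received before randomisation as ineligibility; the patient is not randomised.
2. After randomisation, record receipt and its time, keep the patient in follow-up, collect all outcomes, and analyse her in her randomised group.
3. Define intention-to-treat as all randomised patients and name it the primary analysis for superiority.
4. Use anxiolytic receipt only to define the per-protocol set. For the primary outcome, let it count only if the drug was given before the post-session STAI.
5. State whether drugs given for procedural sedation fall under the rule.

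No change is proposed to any clinical decision about giving anxiolytics. The cost is amendment wording, one time field in the eCRF, and a few medicated patients in the intention-to-treat set, with the per-protocol analysis as the sensitivity check. If these patients are retained with their post-session score, the rule itself costs no sample size.

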### Outcomes

The primary outcome will be the difference between the preoperative anxiety score taken 15 to 20 min before the music-listening session and the preoperative anxiety score taken shortly after the session, as measured with the STAI (State-Trait Anxiety Inventory) for state anxiety [22]. We will use the mean change score from baseline to post music intervention to compare groups. The STAI is a validated and widely used questionnaire for measuring patient anxiety, in particular in the context of music therapy. This self-assessment questionnaire consists of 40 statements, each describing an attitude. It is composed of two separate sections of 20 statements each: The first section assesses trait anxiety and the second measures state anxiety. In each section, ten statements express a negative attitude (e.g. ‘I am worried’) and the other ten express a positive attitude (e.g. ‘I feel calm’). In the section measuring trait anxiety, participants answer each item to report the frequency of their feelings. All items are rated on a Likert-type 4-point scale ranging from ‘almost never’ to ‘sometimes’, ‘often’, and ‘almost always’. In the section measuring state anxiety, participants answer each item to report the intensity of their feelings in the preoperative situation. All items are rated on a Likert-type 4-point scale ranging from ‘not at all’ to ‘somewhat’, ‘moderately so’, and ‘very much so’. STAI results are obtained by adding the scores for negatively worded items and subtracting the scores for positively worded items. Total scores for trait and state anxiety range between 20 and 80: The higher the score, the more the patient is anxious for both types of anxiety. The time needed for the patient to take the test is between 10 and 15 min.

In our study, we will use the validated French version of the STAI (‘Inventaire d’Anxiété Situationnelle et de Trait d’Anxiété’ (IASTA)) [23]. Patients will be asked to fill the first section of the self-assessment questionnaire (trait anxiety) the day before surgery, during the inclusion visit. The day of surgery, they will be asked to fill the second section (state anxiety), which assesses ‘how the individual feels now, at this moment, in terms of concern, tension or nervousness’. A department nurse will administer the questionnaire 15 to 20 min before the start of the music-listening session, and will do so a second time shortly after the session has ended.

There will be four secondary outcomes in our study. The first will be the difference between the preoperative anxiety score before the music-listening session and the preoperative anxiety score after the session, as measured with the visual analogue scale (VAS). The VAS is a calibrated plastic stick that can be used horizontally or vertically. A slider moves along the plastic stick on the side presented to the patient, with the words ‘calm, not at all anxious’ appearing on one end of the stick and the words ‘extremely anxious’ appearing on the other. The patient must place the slider in the position that better describes their level of anxiety. On the other side of the stick is a graduation scale, which is seen only by the care provider. The latter reads the patient’s level of anxiety on a scale from 0 to 10 based on the slider position selected. Studies have shown that anxiety levels measured with the VAS are significantly correlated to those measured with the STAI questionnaire.

In our study, a department nurse will collect VAS values for each patient. Before administering the test, the nurse will explain to the patient how the scale works and will make sure that she understands the information. The test will be administered 15 to 20 min before the start of the music-listening session, and a second time shortly after the session has ended (i.e. after the patient has filled the second section of the STAI self-assessment questionnaire and before she goes to the operating room).

The second secondary outcome will be the difference in pain values in immediate post surgery between the intervention group (patients listening to self-selected music) and the control group (patients listening to predetermined music), as measured with a numerical scale (NS). This self-reported scale is administered by asking the patient to rate their level of pain from 0 (no pain) to 10 (worst pain). In our study, a nurse will measure NS values 30 min after the patient has returned from the operating room.

The third secondary outcome will be the difference in preoperative physiological parameters (heart rate and systolic/diastolic blood pressure) measured before and after the music-listening session. A nurse will record these parameters 15 to 20 min before the session, after she administers the STAI and VAS tests, and will do so again shortly after the session, after she administers the STAI and VAS tests a second time and before the patient goes to the operating room. Physiological parameters will be measured in the Gynaecological Surgery Department with an automatic electronic tensioning device (reference: CRITICARE EQUALITY Series 506DN Comfort plus®) consisting of an adult-size inflatable Velcro armband. The armband size will be adapted to the patient’s arm (different sizes are available in our department). The blood pressure of each patient will be taken at 7.00 a.m. The patient will be informed that she must remain calm in the room for at least 10 min before measurements are taken. Physiological parameters will be measured with the patient relaxed in a supine position, on a bare arm with the crook of the elbow placed at the level of the heart. When attaching the armband, the nurse will make sure that the measurement sensor faces the brachial artery. Blood pressure will not be measured on a perfused or injured arm, on an arm with an arteriovenous fistula, or on an arm that has undergone lymph-node dissection. Blood pressure will be recorded in millimetres of mercury and heart rate will be recorded in beats per min.

The fourth secondary outcome will be hospital length of stay from hospital admission to hospital discharge.

The assessment of each outcome and the timing are resume in the Figs. 1 and 2.

